	**Study period**			
	**Enrolment/allocation**	**Post-allocation**		
**Time point**	Baseline (at allocation or by telephone)	1 week (telephone)	6 weeks (outpatient clinic)	6 months (telephone)
**Eligibility screen**	X			
**Informed consent**	X			
**Allocation (RBL/SCL)**	X		X	
**Primary outcomes**				
HD symptoms (PROM)	X	X	X	X
Abscess			X	
Urine retention			X	
Anal stenosis			X	
Incontinence			X	
Fistula			X	
Recurrence			X	X
**Secondary outcomes**				
Satisfaction/experience (PREM)		X		
Absenteeism		X	(X)	
Number of treatments			X	X
Crossover rate				X

### Sample size calculation

The sample size is based on a success percentage of 70% in both treatment arms, in terms of symptom reduction. Based on the available literature from Cocorullo et al. [6], we will perform a non-inferiority analysis with a two-sided significance (alpha 2.5%), 80% power and a 10% non-inferiority limit. Consequently, a total of 330 randomised patients are required per arm, so 660 randomised patients in total.Significance level (a) = 2.5%Power (1-beta) = 80%Non-inferiority limit = 10%Proportionality group A = 70%Proportionality group B = 70%Sample size required per group = 330Total sample size required = 660

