## Statistical analysis

Both intention-to-treat and per-protocol analyses shall be carried out. Crossover is not desirable, but possible if deemed necessary by the treating physician. Crossover will be considered as a secondary outcome measure. Analyses will be carried out using SPSS version 26.0. A *p*-value of 0.05 or less is considered as statistically significant.

For the primary outcome, any reduction in a PROM/PREM score per symptom is scored as ‘improvement’ when considering the results as binary success or not. Analysis of primary outcomes will be tested with chi-square test or Fisher’s exact test. Considering there are four time points for the outcomes, these time points will be taken into account during the analysis. Descriptive methods will be used to check the quality of the data, homogeneity of the two treatment groups and primary and secondary endpoints. Significant confounders will be identified using multivariate analysis. Categorical variables will be presented as percentages and continuous variables will be presented as means with their confidence intervals. To examine gender differences, an additional analysis will be carried out. An interim analysis will take place after the first 300 patients have been randomised and 6-month follow-up is completed. Both the number of patients who experienced complications and the number of patients with recurrent symptoms after 6 months will be evaluated between the two groups. If there are significant differences, then the entire study group will discuss these findings and discuss whether the study can be continued.

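### The non-inferiority alpha is labelled two-sided 2.5%, but 330 per arm and 80% power follow from one-sided 2.5%; the label needs correcting, the sample size does not

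*Protocol article*

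**What the plan says.** The protocol article's section on the sample size calculation sets the design: "The sample size is based on a success percentage of 70% in both treatment arms, in terms of symptom reduction". It continues that "we will perform a non-inferiority analysis with a two-sided significance (alpha 2.5%), 80% power and a 10% non-inferiority limit", and concludes that "a total of 330 randomised patients are required per arm, so 660 randomised patients in total". The list of inputs that follows repeats the level as "Significance level (a) = 2.5" per cent, this time with no sidedness, beside 80% power and a 10% limit.

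The statistical analysis section gives one general threshold: a p-value "of 0.05 or less is considered as statistically significant". It does not say whether this is one- or two-sided, makes no exception for the non-inferiority comparison, and does not mention 2.5%. The tests it names for the primary outcomes are the chi-square test and Fisher's exact test.

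No loss to follow-up enters the calculation. Follow-up runs to 6 months, participants may withdraw at any time (consent procedure), and both intention-to-treat and per-protocol analyses are planned.

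**The concern.** A non-inferiority comparison uses one tail: the question is whether sclerotherapy is worse than rubber band ligation by the margin or more. An alpha of 2.5% described as two-sided puts 1.25% in that tail and corresponds to a 97.5% confidence interval. An alpha of 2.5% described as one-sided corresponds to the usual 95% interval. The article states the first, and its sample size comes from the second.

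This level decides whether non-inferiority is declared. If the sentence that defines it cannot be matched to the sample size or to the analysis threshold, the criterion is open to interpretation once results are known. It also leaves unclear what the 80% power refers to. The same section presents the formula result as the number to be randomised, so the stated power requires an outcome from every randomised patient.

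**Working it through.** **Inputs** (all from the sample size section): success 70% in each arm, margin 10 percentage points (read as absolute), power 80%, alpha 2.5%. Allocation is 1:1 (trial design).

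**Formula** (unpooled normal approximation, per arm):

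n = (z_α + z_β)² × [0.7×0.3 + 0.7×0.3] / 0.10² = (z_α + z_β)² × 42, with z_β = 0.8416.

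**Reproducing the plan's figure.** One-sided 2.5%, z_α = 1.960: (2.8016)² × 42 = 329.65, so 330 per arm and 660 in total. This matches the article exactly.

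**The level as written.** Two-sided 2.5%, so 1.25% in the tested tail, z_α = 2.2414: (3.0830)² × 42 = 399.2, so 400 per arm and 800 in total.

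**Power with 330 per arm.** The standard error of the difference is √(0.42/330) = 0.03567, so 0.10/0.03567 = 2.803.

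| Level | z_α | Power = Φ(2.803 − z_α) | n per arm for 80% |
|---|---|---|---|
| One-sided 2.5% | 1.960 | 80.0% | 330 |
| Two-sided 2.5%, as written | 2.241 | 71.3% | 400 |

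**Does another method rescue the label?** For two-sided 2.5%, the Farrington-Manning method gives 399 per arm and a continuity correction gives 420. Neither is 330. For one-sided 2.5%, Farrington-Manning gives 329, in line with the article.

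**Effect on the decision.** With 330 per arm and success near 70%, non-inferiority is declared if the observed deficit is smaller than 0.10 − z_α × 0.03567:

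- one-sided 2.5%: 0.10 − 0.070 = about 3.0 points
- two-sided 2.5%: 0.10 − 0.080 = about 2.0 points

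An observed deficit of 2.5 points would pass under the first and fail under the second.

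**Loss.** The unrounded result is 329.65, so rounding to 330 leaves no room for missing outcomes. The documents give no loss rate; the losses below are assumptions. At one-sided 2.5%, power = Φ(0.10/√(0.42/n) − 1.960):

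| Assumed loss | Analysed per arm (330 × (1 − loss)) | Power |
|---|---|---|
| 5% | 313.5 | 78.0% |
| 10% | 297 | 75.8% |
| 15% | 280.5 | 73.4% |
| 20% | 264 | 70.8% |

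**The case against.** The best defence is that the calculation is right and only one word is wrong. The exact match at one-sided 2.5% is strong evidence of what was meant, and the input list gives 2.5% without a side. This stands. A reader might infer from the 400 per arm and 71.3% that the trial is too small, but those figures apply only if 1.25% in the tested tail was really intended, and nothing else in the article suggests that.

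A second defence concerns the 0.05 threshold. It is attached to chi-square and Fisher's exact tests, the first non-directional and the second conventionally two-sided. A two-sided 5% test has 2.5% in each tail, so the two sections agree once the label is corrected. This also stands. A reader might take 0.05 as a third, one-sided level with a 90% interval, which would need only 260 per arm and give 87.7% power at 330. The article does not support that as an intended level. What remains is that the sidedness is unstated and that, against the label as printed, the two sections do disagree.

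Third, the article condenses a full protocol that is not shown and may deal with attrition. No time point is fixed as primary, so loss at the 6-month call is not necessarily the relevant loss. Crossover after two treatments is permitted and need not remove patients from the per-protocol set. These points limit the loss argument to a clarification. They do not change the fact that the article's own number includes no allowance and is described as randomised.

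Finally, the analysis section describes no comparison with the margin at all. That is a separate matter, but it means the corrected level has to be written into that section; there is no existing statement of it to amend.

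**Conclusion.** The point holds as a labelling error in the sentence that defines the confirmatory level. With 70% success in both arms, an absolute margin of 10 points and 80% power, 330 per arm follows from one-sided 2.5%. Two-sided 2.5% as printed would need 70 more per arm (400 against 330), or would leave power at 71.3%, 8.7 points below the stated 80%. As printed, it also does not match the 0.05 threshold of the analysis section.

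This is not evidence of a wrong sample size or of an underpowered design. With the label corrected and 0.05 read as two-sided, the sections agree and the stated power is right for 330 analysed per arm.

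The loss point is secondary. The 80% holds for complete data; how far it falls depends on a loss rate that the documents do not give. A reader might take about 76% as the trial's true power, but that figure rests on an assumed 10% loss and is only an illustration.

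**What to change.** In the sample size section, replace the two-sided label: state a one-sided alpha of 2.5%, equivalent to comparing the lower limit of the two-sided 95% confidence interval for the difference in success (sclerotherapy minus rubber band ligation) with −10 percentage points.

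In the statistical analysis section, name that level for the non-inferiority comparison, and state that the 0.05 threshold is two-sided.

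In the sample size section, also say that 80% power refers to 330 patients analysed per arm, and add the power at the loss the sponsor itself expects. The 5% to 20% range shown above is not a substitute for that figure.

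The cost is text only. The sample size, margin and conduct are unchanged; the one less favourable consequence is that the power quoted for 660 randomised patients will fall somewhat below 80% if any loss is expected.

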### Recruitment and blinding

In the Netherlands patients with HD are mostly referred to the surgeon by their general practitioner. The outpatient clinic nurses or researchers will screen for eligibility and send the patient written information (study information folder (PIF) and plan their appointment at the outpatient clinic. This allows for a minimum of 48 h to reflect on the information. The patient takes the information to the outpatient clinic appointment to discuss with the treating physician. In the case of participation, oral and written consent are gathered.The treating physician generates the allocation process or registration to the preference arm, after written informed consent has been provided.The randomization sequence will be computer generated with the Castor^EDC^ program (version 24.41) without stratification, with 1:1 allocation to either group, generating a unique record number.Both patient and treating physician are not blinded for the treatment arm.In concept, the researcher who completes the telephone interviews at 7 days and 6 months is blinded to the given therapy and is instructed not to actively ask patients which treatment they received. However, the data is added in the same database system, so complete blinding is not guaranteed. The physician at T = 0 and T = 6 weeks is not blinded as it is otherwise impossible to complete the treatment. Also, at 6 weeks the treating physician should repeat the initial treatment when necessary, following protocol.

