## Methods and analysis

### Trial design

The THROS trial is a non-inferiority, multicentre, randomised controlled trial with two parallel groups: RBL vs. SCL. The allocation ratio is 1:1. Crossover is possible for patients who experience no improvement of symptoms after at least two treatments within one treatment arm. It is expected that when two treatments have not reduced symptoms and a third treatment is necessary, both patients and surgeons are inclined to try a new treatment option. So crossover rate is also indicative for treatment success. Also, when patients have a strong preference for one of the two treatment arms and refuse randomisation, then registration in the preference arm is allowed. All patients’ symptoms could not be effectively managed by conservative treatment, which included dietary changes, laxatives, and lifestyle improvements. Conservative management was the first step of therapy in all cases. After eligibility has been established and patients have given their written informed consent, allocation or registration to one of the two treatment arms is possible. Data will be analysed on both ‘intention to treat’ and ‘per protocol’ basis.

The trial was registered at the Dutch Trial Register (NL8377). The protocol was drafted in accordance with the Standard Protocol Items: Recommendations for Interventional Trials statements (SPIRIT) [12].

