### Eligibility criteria

#### Inclusion criteria

Grade 1 (symptomatic with rectal blood loss) or grade 2 haemorrhoids (Golligher classification)Aged 18 years old or older and legally competent

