### Data collection

Each participating centre’s personnel involved in treating patients with HD are trained in providing eligible patients with both oral and written information about the study. All the medical baseline and procedure data are collected at the individual hospitals. The data is stored in standardized case record forms (CRFs) within Castor.

The surgeons involved in treating patients with HD are responsible in collecting the data from the initial visit/treatment and the 6-week outpatient visit where complications are scored. Research personnel of each participating centre is responsible for their own data collection during the 6-month follow-up period.

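### Unstratified allocation followed by an unadjusted primary test leaves out centre and haemorrhoid grade, both known beforehand: valid, but a little precision and within-centre balance are given away

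*Protocol article*

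**What the plan says.** Trial design describes a "non-inferiority, multicentre, randomised controlled trial with two parallel groups: RBL vs. SCL" and states that "The allocation ratio is 1:1". Recruitment and blinding adds that the computer-generated sequence is "without stratification, with 1:1 allocation to either group". The article gives no reason for having no strata.

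Two candidate strata are available at that moment. Centre is known by definition. Grade is an inclusion criterion, "Grade 1 (symptomatic with rectal blood loss) or grade 2 haemorrhoids", and the order of steps is "After eligibility has been established and patients have given their written informed consent, allocation or registration", so grade is recorded before the arm is assigned.

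Statistical analysis names chi-square or Fisher's exact test for the primary outcomes. It also plans a descriptive check that the groups are homogeneous and a multivariate analysis to identify significant confounders. Neither names centre or grade.

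**The concern.** Some outcomes pass through local hands. The unblinded treating physician decides whether treatment is repeated and whether crossover is needed, and surgeons collect the data at "the 6-week outpatient visit where complications are scored". Grade 1 patients must have blood loss to enter and grade 2 patients need not, so baseline symptoms may differ by grade, while success is any fall in symptom score.

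If centre or grade predicts outcome, unstratified allocation lets the arms differ on it by chance, and an unadjusted test does not remove that difference. The trial would then have a slightly wider confidence interval than necessary and possibly lopsided arms within small centres. This is a stated choice about allocation. An analysis plan that is not shown could add covariates, but it could not change how patients were assigned.

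**Working it through.** **Inputs from the article.** Success 70% in each arm, 10-point margin, 80% power, 330 per arm (Sample size calculation). The error rate is worded as "two-sided significance (alpha 2.5%), 80% power and a 10% non-inferiority limit".

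**1. The plan's own figure.** With z-values 1.96 and 0.8416 (2.5% one-sided, 80% power) and variance 0.7 × 0.3 = 0.21:

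n = 2 × 0.21 × (1.96 + 0.8416)² / 0.10² = 329.7, so 330 per arm.

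The figure reproduces if the 2.5% is read as one-sided; 1.25% per side would need 400. The SE is √(2 × 0.21/330) = 3.57 points, and power is Φ(0.10/0.0357 − 1.96) = 80.0%. The calculation uses the full variance of 0.21, which already contains any variation between centres and grades. Unstratified allocation therefore delivers the planned power.

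**2. Validity.** In simulation of the unstratified, unadjusted comparison, with grade gaps of 10 and 20 points, one-sided type I error was 2.7% and 2.5%. That is nominal within simulation error.

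**3. What stratification could remove.** The documents give no number of centres, grade mix, grade effect or centre effect, so these are assumptions. Take grades 50:50, a success gap d between grades, and a between-centre SD s:

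- between-stratum variance B = 0.25d² + s²
- SD of the chance prognostic difference between arms = √(2B/330)
- power with stratified allocation and a matching analysis = Φ(0.10/√(2(0.21 − B)/330) − 1.96)

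| Assumption | B | Share of 0.21 | Chance-shift SD | 95% limit of shift | SE | Power |
|---|---|---|---|---|---|---|
| neither prognostic | 0 | 0% | 0 | 0 | 3.57 | 80.0% |
| d = 10, s = 5 points | 0.0050 | 2.4% | 0.55 | 1.1 | 3.52 | 81.0% |
| d = 20, s = 8 points | 0.0164 | 7.8% | 1.0 | 1.95 | 3.43 | 83.1% |

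(Shift and SE in percentage points.)

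**4. Allocation and analysis separately.** Simulation of 660 patients in the stronger setting gave about 80.1% power unstratified and unadjusted, 81.9% with a stratified analysis alone, and 83.4% with allocation also stratified by both factors. In the weaker setting power went from about 80.3% to 81.1%. Roughly half of the larger gain therefore comes from the analysis alone. Stratifying allocation by centre only, with grade taken into the analysis, should fall between the last two figures.

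**5. Balance within a small centre.** If each patient's arm within a centre behaves like a fair coin toss, P(14:6 or worse among 20) = 2 × P(X ≥ 14), X ~ Bin(20, ½), = 11.5%.

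**The case against.** The strongest reply is that nothing here falls short of plan. Simple 1:1 allocation of 660 patients is unbiased, the sample size already pays for the extra variability, and the documents do not establish that grade or centre predicts success. All of that stands, and it sets the size of the point.

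The reply also has force on cost. The treating physician is unblinded and starts the allocation, and a preference arm is open to patients who decline randomisation. Small blocks within many cells would make the next assignment easier to guess, and a patient could be steered to the preference arm. This argues for few strata and hidden block sizes; it does not argue against stratifying by centre at all.

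Four stronger readings are tempting but not supported:

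- A reader might set a chance shift of 1 to 2 points against the 10-point margin as if it were bias. It is already part of the 3.57-point sampling SD and is covered by the confidence interval.
- A reader might argue that complications, crossover and repeat treatments are too sparse to adjust later. The Introduction cites complication rates of 8–80% and 34–49%, and the Discussion says a single treatment is insufficient in most cases. Sparseness could apply only to individual rare complications.
- A reader might carry the symptom-success figures over to the interim look at 300 patients. That look compares complications and recurrence, and it has no margin test.
- A reader might conclude that local practice drives symptom success. The procedures are described uniformly, and the 6-month score is patient-reported by telephone to a researcher who is intended to be blinded.

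**Conclusion.** The point holds as a minor design improvement. Leaving centre and grade out of both the allocation and the named primary test is valid, inflates no error rate and keeps the stated 80% power. It forgoes about 1 power point if grades differ by 10 points in success and centres have an SD of 5 points, about 3 if these are 20 and 8 points, and nothing if neither factor is prognostic. These effects, and the 50:50 grade mix, are assumptions. Marked imbalance within a small centre is possible but does not by itself bias the overall comparison.

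**What to change.** In Recruitment and blinding, for all patients still to be randomised, stratify the 1:1 Castor allocation by centre, in permuted blocks of randomly varying, undisclosed size. Leave grade out of the allocation strata to avoid thin cells.

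In Statistical analysis, replace the unadjusted primary test with a prespecified risk difference at 6 months and its confidence interval, stratified by or adjusted for centre (small centres pooled) and grade, for instance by Mantel-Haenszel. Compare the interval with the 10-point margin.

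The cost is a setting in Castor and a short amendment, with no extra patients or visits. The downside is slightly more predictable allocation in small centres of an open-label trial with a preference arm; the hidden varying blocks and the single stratification factor limit it. The article does not give recruitment status. If recruitment is far advanced, the adjusted analysis alone still captures part of the gain.

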### Interventions

Eligible patients are randomised via Castor^EDC^ to either the SCL or RBL arm. Patients who deny randomisation are eligible to the preference arm of their choice. Patients who are randomised to receive SCL are treated with 4 cc Aethoxysklerol 3% (polidocanol) in the haemorrhoidal tissue via a small 18 mm proctoscope (Sapimed). Patients who are randomised to receive RBL are treated via the same small proctoscope with 3 rubber bands which are placed at the base of the haemorrhoidal tissue (Barron ligation). When after approximately 6–8 weeks a second treatment is required this should be the same treatment as the first (SCL or RBL), after which, in case of persistence after at least two treatments and again 6–8 weeks in between treatments, a crossover is permitted. There are no restrictions regarding concomitant care during the trial.

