### Participant timeline

Treatment is provided according to the following timeline (Table 2):T = day 0 → outpatient clinic treatment with either SCL or RBL after providing written informed consent to the treating physician.T = day 7 → telephone appointment with a blinded researcher: the PROM and PREM questionnaires are completed by the researcher.T = 6 → weeks outpatient clinic appointment with a physician. The PROM and Wexner incontinence scale are completed together with a physical examination. If needed, the same treatment (SCL or RBL) is repeated.T = 6 → months telephone appointment with a blinded researcher: PROM questionnaire completed and (subjective) symptoms related to recurrence are assessed.

**Table 2 Tab2:** Participant timeline

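### The trial's only blinded assessment, the telephone interview, is conceded to be incompletely blinded because of the shared database, yet the timeline calls the interviewer blinded without qualification

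*Protocol article*

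**What the plan says.** All references are to the protocol article.

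- **Recruitment and blinding** rules out blinding for most roles: "Both patient and treating physician are not blinded for the treatment arm". It adds: "The physician at T = 0 and T = 6 weeks is not blinded as it is otherwise impossible to complete the treatment".
- The same section makes one exception, stated as an intention: "the researcher who completes the telephone interviews at 7 days and 6 months is blinded to the given therapy". The safeguard given is that this person "is instructed not to actively ask patients which treatment they received".
- It then limits the exception: "the data is added in the same database system, so complete blinding is not guaranteed".
- **Participant timeline** describes both calls as made by a blinded researcher and does not repeat the limit. The 6-month entry reads: "telephone appointment with a blinded researcher: PROM questionnaire completed and (subjective) symptoms related to recurrence are assessed". The 1-week call covers the PROM and the PREM.
- **Interventions** puts randomisation in the data system: "Eligible patients are randomised via Castor". **Data collection** places the case record forms in the same system and assigns follow-up locally: "Research personnel of each participating centre is responsible for their own data collection during the 6-month follow-up period".

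**The concern.** When patients cannot be blinded, the person who asks the questions and enters the answers is the remaining source of bias that the design can control. Here that person collects primary outcomes. Recurrence at 6 months also feeds the interim comparison on which the study group would discuss whether the trial can continue.

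The binary success rule makes small shifts count. Any fall in the PROM score is an improvement, so one point on one Likert item can change a patient's classification. In a non-inferiority trial, bias in either direction does harm: towards sclerotherapy (SCL) it makes a false claim of non-inferiority more likely, and against SCL it costs power.

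The protocol names the shared database as the reason why blinding cannot be guaranteed. That is a matter of arrangement, unlike the blinding of patients or of the treating physician.

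**Working it through.** **1. Who is blinded, and for which outcome**

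| Contact | Who collects | Blinded? | Primary outcomes collected |
|---|---|---|---|
| 1 week, telephone | Researcher | Intended, not guaranteed | PROM |
| 6 weeks, clinic | Physician | No | PROM, complications, recurrence |
| 6 months, telephone | Researcher | Intended, not guaranteed | PROM, recurrence |

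The telephone interview is therefore the only blinded assessment.

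**2. Routes by which the arm could become known**

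- *Database.* Randomisation and case record forms are both held in Castor, and the article itself says that this leaves blinding incomplete.
- *PREM at 1 week.* The Appendix asks about pain during and after treatment and about urge. The Introduction lists urgency and pain among the main disadvantages of rubber band ligation (RBL). No item asks what was done, but the answers may hint at it. This route exists only at 1 week.
- *Treatment history at 6 months.* Number of treatments and crossover are recorded at 6 months, which in Table 2 is the telephone contact. If they are asked in the call, the treatment is likely to come up. The article does not say whether they come from the call or from the record.
- *Local staff.* Each centre's own research personnel do the follow-up, and researchers may also screen patients.

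**3. The plan's own figure**

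Inputs from Sample size calculation: 70% success in both arms, margin 10 points, power 80%, alpha 2.5% (taken as one-sided).

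n per arm = (1.960 + 0.842)² × (0.70 × 0.30 + 0.70 × 0.30) / 0.10² = 7.849 × 0.42 / 0.01 = 329.7, so 330. This reproduces the stated figure. Better blinding changes none of these inputs.

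**4. Illustration of scale (assumed inputs)**

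The documents give neither an interviewer effect nor an SD of change. Assume a normally distributed change in total score with 70% success (z = 0.524) and a mean shift of 0.5 points in one arm only. The shift in success is Φ(0.524 ± 0.5/SD) − 0.70.

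| Assumed SD | Shift upwards | Shift downwards |
|---|---|---|
| 3 | Φ(0.691) − 0.70 = +5.5 points | Φ(0.357) − 0.70 = −6.0 points |
| 4 | Φ(0.649) − 0.70 = +4.2 points | Φ(0.399) − 0.70 = −4.5 points |
| 5 | Φ(0.624) − 0.70 = +3.4 points | Φ(0.424) − 0.70 = −3.6 points |

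The assumed shift drives the result. With 0.25 points and SD 4, Φ(0.524 + 0.0625) − 0.70 = +2.1 points; with no shift, or an equal shift in both arms, the difference is about zero.

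**5. What a differential bias b would do at 330 per arm**

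- False non-inferiority at a true 10-point deficit (70% v 60%), bias towards SCL: Φ(b/s − 1.96), with s = √{[0.70 × 0.30 + (0.60 + b)(0.40 − b)]/330}.
- Power with truly equal arms, bias against SCL: Φ((0.10 − b)/s′ − 1.96), with s′ = √{[0.21 + (0.70 − b)(0.30 + b)]/330}.

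| Assumed b | False non-inferiority | Power |
|---|---|---|
| 0 | 2.5% | 80% |
| 2 points | 7.8% | 60% |
| 3 points | 12.7% | 49% |
| 5 points | 27.9% | 28% |

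These rows show how sensitive the conclusion is to a given b. They do not say that any b is present.

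**The case against.** The strongest reply is that the limit is disclosed. The blinding section says plainly that interviewer blinding is an intention and not guaranteed, the timeline wording can be read as shorthand, and access roles are data-management detail that an article may leave to the full protocol. This stands in part: the absence of access settings from the article is not a fault. The point rests on the stated concession, which concerns primary outcomes and has an identified cause.

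Second, the interviewer's influence is limited. The PROM consists of five fixed items, and recurrence is defined as the subjective return of symptoms. Both are reported by patients who know their treatment, and the 6-week PROM is taken by an unblinded physician. Bias from patients' expectations would survive perfect interviewer blinding. This stands, and it caps what any fix can achieve.

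Third, the size rests wholly on assumption, including a shift confined to one arm and a total-score rule, although Statistical analysis scores improvement per symptom. This also stands; the figures are illustrative.

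A reader might go further and infer that the entry screen displays the allocation, that blinding has been abandoned, or that the interviewer decides whether there is a recurrence. The documents support none of these. They say only that the data go into the same system, they keep blinding as the aim with an instruction not to ask, and they give the interviewer no adjudicating role.

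**Conclusion.** The point holds in a limited form. The only blinded assessment in the trial covers primary outcomes and is, by the protocol's own statement, incompletely blinded because of the shared database. The unqualified description in the timeline should be brought into line with the blinding section.

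The size of any resulting bias cannot be derived from the documents. The 3 to 6 points depend on an assumed half-point shift in one arm and an assumed SD of 3 to 5. They show that a modest interviewer effect could matter against a 10-point margin, and should not be read as an estimate. The sample size stays at 330 per arm. This is a cheap improvement and does not invalidate the design.

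**What to change.** 1. Give telephone interviewers a database entry role without the allocation and procedure pages.
2. Open each call by asking the patient not to name the treatment.
3. Ask the PROM and recurrence questions first, before the PREM and before any question on number of treatments or crossover. Alternatively, have someone else already on the team take those two items from the record.
4. At the end of the call, record whether the interviewer learned the arm, and use this in a sensitivity analysis.
5. If this is not done, describe the assessment as not reliably blinded, in the timeline as well as in the blinding section.

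The cost is a small amount of database set-up and one extra item; the documents give no costing, so this is a judgement. No extra staff should be needed, but where the same local person screens and interviews, the access role alone will not keep the arm hidden. Protection remains partial in any case, because the reporting patients and the 6-week physician are unblinded.
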